# Evaluation of smartphone APP-based case-management services among antiretroviral treatment-naïve HIV-positive men who have sex with men: a randomized controlled trial protocol

**DOI:** 10.1186/s12889-020-8171-5

**Published:** 2020-01-20

**Keywords:** HIV, Men who have sex with men, mHealth, Case management, Adherence

## Abstract

**Background:**

Men who have sex with men (MSM) are disproportionally affected by HIV in China. ‘Treatment as Prevention’ is a promising strategy for HIV prevention but requires adequate adherence. Mobile health (mHealth) may be an acceptable and feasible approach for service delivery, but there is little evidence supporting mHealth intervention for improving antiretroviral treatment adherence among HIV-infected MSM in low- and middle-income countries, including China. This study will aim to develop a smartphone application-based case-management service and compare its efficacy to standard care with regards to adherence, CD4, HIV viral load and psychosocial outcomes among MSM patients in Guangzhou, China.

**Methods:**

A non-blinded 1:1 parallel-group randomised controlled trial will be conducted in Guangzhou Eighth People’s Hospital, with 300 MSM enrolled in each arm. Eligible MSM who are newly initiating ART will be randomly assigned to an intervention group (standard-of-care case management plus mHealth intervention) or a control group (standard-of-care case management). The development of the mHealth intervention will be based on the information–motivation–behavioural skills theory of ART adherence, and comprise four components: educational articles, one-to-one online communication with case managers, support-service information and hospital-visit reminders. Outcome measures will be collected at baseline and at months 1, 3, 6, and 12. The primary outcomes will be ART adherence and CD4 count at month 6. Secondary outcomes include HIV RNA, sexual behaviours, mental health status, illness perceptions, and quality of life. *χ*^*2*^ test and t-test will be used for between-group comparisons. Intervention effects will be evaluated using General estimating equation performed by SAS 9.0, on the principle of intention-to-treat. Structural equation modelling will be used to test potential mechanisms of intervention effect.

**Discussion:**

This study is the first to explore the efficacy of mHealth intervention in the case management services targeted at HIV-infected MSM in low-and middle-income countries. Once proven effective, the innovative mHealth service could be integrated into the routine case management of PLWH. as well as be tailored to the patient management service for other chronic conditions.

**Trial registration:**

ClinicalTrial.gov: NCT03860116; Registered on 1 March 2019.

## Background

Men who have sex with men (MSM) have been identified as one of the key populations in the HIV epidemic. The prevalence of HIV among MSM in China has been rapidly and continuously increasing, especially in metropolitan cities such as Beijing, Guangzhou, and Chengdu [1–3]. The pooled prevalence of HIV infection among MSM soared from 1.4% in 2001 to 9.0% in 2013 [4], and transmissions between MSM accounted for 25.5% of the new HIV infections in 2017 [5].

‘Treatment as Prevention’ (TasP) is a promising strategy for HIV prevention and control. In 2016, the Chinese Centre for Disease Control and Prevention (CDC) revised the national guidelines for antiretroviral treatment (ART) and suggested immediate treatment for all people living with HIV/AIDS (PLWHA) [6]. However, the long-term success of such efforts to scale-up coverage of ART for PLWHA may be negatively affected by deficits in adherence to the spectrum of HIV care. ART requires adequate adherence (usually defined as intake of at least 95% of ART doses [7, 8]) to yield satisfactory clinical outcomes, e.g., suppressing HIV viral replication [9], improving quality of life [10], and preventing transmission [11]. However, a recent meta-analysis indicated that only 77.6% (95% confidence interval [CI]: 71.6–83.1) of Chinese PLWHA on ART maintained adequate adherence [12]. Barriers to ART adherence include patient factors (e.g., education, lack of self-efficacy, mental illness), medication factors (e.g., side effects, pill burden, and food requirement), and system of care (e.g., linkage of care, negative experiences of healthcare system) [13–15]. Moreover, MSM can experience a fear of disclosure in public and healthcare settings and the stigma associated with their sexual orientation [16]. Thus, the ART adherence of this group warrants more attention.

Case management has been regarded as a routine practice to address the complex medical barriers to and needs for ART adherence [17, 18]. It incorporates a wide range of medical and supportive services and is routinely used in many countries. It has been shown to be effective in increasing CD4 counts [19], and in improving care engagement, ART adherence and quality of life [20, 21], as well as in reducing transmission-risk behaviours among PLWHA [22]. Concurrently, the development of information technology has led to a paradigm of mobile health (mHealth), which is characterized by the communication and delivery of health services via text messages, smartphone applications (APPs), websites, and social media. Consequently, mHealth has become a highly accessible and adaptive approach to medical practice, especially in low- and middle-income countries [23]. Currently, smartphones are used by 68% of the population in China [24], with up to 97.5% of MSM having a smartphone [25]. Adherence-supporting interventions incorporating mHealth have shown good acceptability and feasibility in HIV-positive MSM [26], and demonstrated efficacy in improving PLWHA’s linkage to care, retention in treatment and adherence to ART [27, 28]. However, to the authors’ knowledge, mHealth interventions to improve the adherence of HIV-positive MSM to ART and potential mechanisms of how an intervention works have not been fully explored in China, and many mHealth interventions have mainly relied on text messages [29]. Thus, there is a need for a rigorously designed and comprehensive mHealth intervention tailored to Chinese HIV-positive MSM.

In addition, it has been suggested in reviews that theory-based behavioural interventions are more likely to be effective than non-theory-based interventions [30]. The Information-Motivation-Behavioural Skills (IMB) model of ART adherence, for example, is widely used to understand the dynamics of ART adherence and to intervene with patients to promote better adherence [31]. This model has been effectively tested across diverse populations worldwide [32–35] and has often been used to guide the development of interventions to promote HIV-related healthy behaviour, such as ART adherence, retention and safe sex [36–39]. According to the IMB model, information on HIV and ART interacts with an individual’s motivation to take ART medication, thereby influencing the development of behavioural skills related to adherence; in other words, well-informed and motivated patients with adequate skills for enacting adherence-related behaviours will exhibit better adherence [40]. Further, psychological functioning (e.g., depression) and access to care are moderating factors in the associations between predictors and adherence outcomes [31] (Fig. 1).

**Fig. 1 Fig1:**
[figure not shown]
Theoretical framework

The objective of this study is to design and evaluate the efficacy of an APP-based case-management intervention among MSM who are newly initiating ART, using the IMB model as the theoretical framework. We have trained nurses to deliver the intervention, and here we describe the protocol of what will be an ongoing open-label randomised controlled trial. The SPIRIT guidelines were adhered to for reporting this manuscript.

## Methods

### Study aim and design

This is a single-centre, parallel-group, open-label randomised controlled trial. We have designed a comprehensive smartphone APP-based case-management service model for MSM newly initiating ART, and will evaluate its efficacy compared to standard-of-care (SOC) case-management services in improving ART medication adherence, HIV clinical indicators, and psychosocial outcomes. The collaborative technology company Trusted Doctor Inc. has developed a smartphone APP (‘Trusted Doctor’) that is linked to WeChat. WeChat is the most popular social media platform in China and has more than 1.1 billion active users according to Tencent Inc.’s 2019 annual report; 93% of the residents in the major cities of China use WeChat every day [41].

This study will be based on the combination of ‘Trusted Doctor’ and WeChat by establishing a link, called *WeChat official account*, between the two smartphone APPs. Certified health care providers (HCPs; i.e., doctors, nurses, or case managers) can use the ‘Trusted Doctor’ APP to have direct and instantaneous online interactions with patients. And patients can use the WeChat platform to access their health care providers, as well as receive services including article alerts, follow-up questionnaires, appointment reminders, free phone calls, etc.

### Study setting

The study is being conducted in Guangzhou, the capital city of Guangdong Province in the southeast of China. HIV prevalence among MSM in Guangzhou increased from 3.9% in 2009 to 11.4% in 2013 [42]. By the end of 2018, 10,453 HIV cases had been reported in Guangzhou and 9161 PLWHA (87.6%) were undergoing ART (data extracted from China’s National Information System of HIV/AIDS prevention and treatment). Participant recruitment and implementation of this study is in cooperation with Guangzhou Eighth People’s hospital, the first authoritative hospital for ART provision in Guangdong. The hospital has provided > 18,000 PLWHA from all around the country with ART and follow-up supportive services and has been exploring the use of case-management services for PLWHA since 2018, in the form of educational sessions and periodic physical visits. Supportive counselling is also provided, if necessary.

### Participants

#### Eligibility criteria

The participant inclusion criteria are as follows: 1) male, aged ≥18; 2) HIV-positive; 3) ART-naïve, and planning to initiate ART on the day of recruitment; 4) self-reported to be HIV-infected through homosexual transmission; 5) having access to the Internet on a smartphone; 6) having a WeChat account and using it in daily communication; 7) willing to provide written informed consent. Participants who have been hospitalized due to severe opportunistic infections are excluded.

#### Recruitment, enrolment and randomization

Potential participants are being recruited from the collaborative hospital that provides ART for PLWHA. Four nurse case managers with previous experience of case management are responsible for participant recruitment and intervention delivery. Before the commencement of this study, all nurse managers received two four-hour training sessions on recruitment, data collection, intervention specification, and tutoring about the APP. After nurse case managers confirm their eligibility and obtaining written informed consent, participants are invited to complete baseline assessments and then randomly assigned to intervention (SOC + mHealth) or control groups (SOC) in a 1:1 allocation ratio. Block randomization (block length = 4) is adopted and random numbers are generated with SAS 9.4.

Written records of group-assignments are sealed in individual opaque envelopes marked with study identification numbers. The intervention group then receive brief training in use of the WeChat program official account from the investigators and are reminded to not forward the WeChat platform to others, to avoid potential confounding effects. Both the control and intervention group are required to ‘friend’ the research team’s WeChat account for data collection and to provide user feedback. Participants’ enrolment information including name, research ID (RID), medical ID, phone number, and their case managers, are documented. The research ID is composed of a skewed date (month plus one) and the sequence of the intraday enrolment to ensure confidentiality. All participants are encouraged to refrain from seeking other health interventions during the active study period. Standard operating procedure (SOP) and program manuals have been developed to guide the study.

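### A fixed block of 4 in an open-label, single-centre trial, with nurses who both recruit and deliver the intervention, leaves up to a third of allocations deducible; vary the block size and withhold it from recruiters

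*Protocol article*

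**What the plan says.** All of this comes from the protocol article.

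- Sequence (Recruitment, enrolment and randomization): "Block randomization (block length = 4) is adopted and random numbers are generated with SAS 9.4". Participants are "randomly assigned to intervention (SOC + mHealth) or control groups (SOC) in a 1:1 allocation ratio". No variation of block length is mentioned.
- Design (Study aim and design): "This is a single-centre, parallel-group, open-label randomised controlled trial".
- Staff (Recruitment, enrolment and randomization): "Four nurse case managers with previous experience of case management are responsible for participant recruitment and intervention delivery".
- Order of steps (same section): "After nurse case managers confirm their eligibility and obtaining written informed consent, participants are invited to complete baseline assessments and then randomly assigned".
- Concealment (same section): "Written records of group-assignments are sealed in individual opaque envelopes marked with study identification numbers".
- Participant code (same section): "The research ID is composed of a skewed date (month plus one) and the sequence of the intraday enrolment".
- Status: the section on educational articles reports 132 participants already in the intervention group, and the Discussion says the trial is still running. The sample size section plans 600, 300 per arm.

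The article does not say whether there is one list or one per nurse, whether the nurses know the block length, or whether the number on the envelope is the research ID.

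**The concern.** Prediction in a blocked trial works from allocations already made. In an open-label trial those become visible, and here the people who deliver the app arm are also the people who decide on eligibility and take consent. With a short block of constant length, the end of each block can be deduced from its beginning. An opaque envelope does not prevent this.

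A nurse who can infer the next arm has some room to influence who enters, for instance by how warmly the trial is offered to a patient likely to adhere well. Selective enrolment of this kind would shift the arms before treatment starts. The adherence comparison is sensitive to it: the protocol plans around a difference of 9 percentage points from an expected 89% in the control group.

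**Working it through.** The protocol gives no figure for predictability, so there is nothing to reproduce. The check enumerates the blocks.

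**Inputs from the protocol:** block length 4; ratio 1:1, so two places per arm in each block; planned total 600; 132 in the intervention arm at the time of writing.

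**Assumptions, not stated in the protocol:** the recruiter knows the block length and the position in the block; each earlier allocation is seen with probability q, examined at 1, 0.5 and 0.25.

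**1. Everything seen (q = 1).** There are 4!/(2!·2!) = 6 equally likely blocks. An assignment is certain once one arm has used both its places.

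| Position | Certain | Best guess correct |
|---|---|---|
| 1 | 0 | 1/2 |
| 2 | 0 | 2/3 |
| 3 | 1/3 | 1/3 × 1 + 2/3 × 1/2 = 2/3 |
| 4 | 1 | 1 |

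Certain share = (0 + 0 + 1/3 + 1)/4 = 33.3%. Best-guess success = (1/2 + 2/3 + 2/3 + 1)/4 = 2.833/4 = 70.8%.

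**2. Only part of a shared list seen.** Position 3 is certain if both earlier allocations were seen and agree: q² × 1/3. At position 4, one arm has already used both its places, and the recruiter is certain if both of those were seen: q². The average over the block is (q²/3 + q²)/4 = q²/3.

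- q = 0.5: 0.25/3 = 8.3% certain (simulation of 400,000 blocks: 8.4%); simulated best-guess success 59.9%.
- q = 0.25: 0.0625/3 = 2.1% certain; simulated best-guess success 55.4%.

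If each nurse has her own blocked list, she sees all of it and the share returns to 33.3%.

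**3. Allocations that can still be protected.** Assuming balance, 2 × 132 = 264 randomised and 600 − 264 = 336 remain. The number determinable with certainty would be 336/3 = 112 at the ceiling, 336/12 = 28 if half are seen, and 336/48 = 7 if a quarter are.

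**4. Scale of a possible bias (illustration on an assumed figure).** Suppose every certain slot in the trial were acted on and this shifted expected adherence between arms by 6 to 12 points within those slots. The spurious overall difference would be 6/3 to 12/3 = 2 to 4 points at the ceiling, 6/12 to 12/12 = 0.5 to 1 point if half are seen, and at most 12/48 = 0.25 point if a quarter are.

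**5. Varied blocks.** Under full knowledge, including the lengths, a block of 6 has 25.0% certain (1.5 of 6) and a block of 8 has 20.0% (1.6 of 8). An equal mix of 4, 6 and 8 gives (4/3 + 3/2 + 8/5)/18 = 24.6% at most, and less when the lengths are not known.

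**The case against.** The strongest reply is that one third is a worst case. It needs the block length, the position in the block and all four nurses' allocations. The article does not say the nurses have these, and patients are tied to individual case managers, so each nurse may see only part of a shared list. That stands, and it is why the range runs down to about 2%. Against it, four colleagues in one hospital can readily share what they see, and the block length is now in print.

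The protocol also has real safeguards. Assignment follows consent and baseline assessment, envelopes are sealed and opaque, and investigators take part in baseline assessment and app training, so the nurses may not handle the envelopes. Patients must plan to start treatment on the day of recruitment, which limits deferral to a later slot. These narrow the opportunity but do not remove it, since whether a patient is offered the trial, and how, comes before all of them. Who holds and opens the envelopes is detail an article leaves to its operating procedures, and its absence is not a fault.

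Four stronger readings are tempting, and the document does not support them:

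- That date-based codes stop the envelopes being numbered in advance. The envelope number and the research ID are named separately and never equated; if they differ, serial pre-numbering is possible.
- That the sequence cannot be audited. Date plus order within the day preserves enrolment order, and a one-month shift does not disturb it, so the codes could be compared with the generated list.
- That the primary outcome is wholly subjective. CD4 count, measured by flow cytometer, is also primary.
- That nurses are in fact steering enrolment. Nothing in the article says so.

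**Conclusion.** The weakness is real and lies in a stated design choice: one constant block of 4, no blinding, one centre, and recruiters who deliver the intervention. Its size is up to one third of assignments certain and about 71% guessed correctly, falling to about 8% or 2% certain on a shared list of which half or a quarter is seen. The ceiling applies in full if the nurses pool what they know or if each has her own list.

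A reader might infer that a third of allocations are known in practice, or that any resulting bias is beyond repair. Neither follows. The first rests on unstated conditions. On the second, mental health, eHealth literacy and the information, motivation and skills constructs are measured before assignment, so adjustment could correct part of the bias, though not what is unmeasured. This is a cheap improvement worth making, not a defect that invalidates the trial.

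The envelope point is secondary and conditional. If the envelope number is the research ID, it depends on the enrolment day and the order within it, so it cannot be put on envelopes in list order beforehand.

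**What to change.** From the end of the current block, replace the constant block of 4 with randomly varying block sizes, for example 4, 6 and 8. Someone not involved in recruitment should generate the list and keep the sizes from the nurses. If there is a list per nurse, do this for each list. Report the switch date, so that participants enrolled before and after it can be told apart. Withholding the lengths does most of the work: if they were known and everything seen, up to 24.6% would still be predictable.

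State in the randomization section whether the envelope number is the research ID, and if it is, give the envelopes a separate sequential number in list order.

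The cost is a new list and envelopes for about 336 participants, a short amendment, and slightly looser interim balance: the largest within-block imbalance rises from 2 in a block of 4 to 4 in a block of 8.

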### Intervention

#### Control group

The control group receives SOC service at the hospital, which commences with a 20-min ART education session for MSM patients newly initiating ART. Follow-up hospital visits are then arranged at one, two, three and 6 months after ART initiation. During each hospital visit, patients undergo physical assessment, receive prescription refills, meet with case managers and schedule the date of their next appointment. Case managers track patients’ medication adherence, sexual behaviours, mental health, sleep quality and weight changes to confirm that the current treatment regimen is suitable. Supportive counselling will be provided to patients, if necessary. If the patients display adequate adherence in the initial three-month period, the refill interval will be extended to 3 months, and case managers will then schedule a fourth meeting at 6 months. After that, patients with stable medication-taking and hospital-visiting behaviour will be referred to the non-governmental organization (NGO) *Red Ribbon* for scheduling of prescription refills.

#### Intervention development

The intervention group receive SOC service and additional mHealth interventions. The design of the mHealth intervention is ground in and informed by the IMB model, which is the most widely used conceptual model for ART adherence. The core content of effective interventions must address the underlying determinants of ART adherence, which, according to the IMB model, include access to adherence-related information, motivation, and behavioural skills.

Elicitation research was conducted to clarify the information, motivation, and behavioural factors that underlie adherence or nonadherence in the targeted group. This involved an extensive review of the literature, lengthy conversations with experts in the field, and elicitation work with multiple stakeholders, including ten HIV-infected MSM with different durations of ART, four nurse case managers, three software engineers, and four NGO staff. These inputs were used to tailor the intervention design, delivery, and content to the needs and characteristics of HIV/AIDS patient, and identified four major intervention components: exposure to educational articles, online communication, supportive service information and hospital-visit reminders (Table 1).

**Table 1 Tab1:** Innovative case management service model

Case management	IMB constructs	Service content	Intervention components
Assessment	Motivation	Establishing rapport	Face-to-face communication
Plan	Motivation	Discussing treatment plan	Face-to-face communication
Service	Information	Knowledge regarding HIV/ART	Educational articles
	Information	Knowledge regarding treatment process?	Educational articles
	Information	Information about preventing transmission	Educational articles
	Behavioural skills	Behavioural skills of adherence	Face-to-face/Online communication
	Behavioural skills	How to promote partner testing	Face-to-face/Online communication
	Behavioural skills	Avoidance of risky behaviour	Face-to-face/Online communication
	Mental health	Counselling	Face-to-face/Online communication
	Care connection	STI treatment	Supportive service information
Coordination	Mental health	Psychological support	Supportive service information
	Care connection	Abstinence therapy	Supportive service information
	Care connection	Other social service	Supportive service information
Evaluation	Care connection	Tests results retrieval	Supportive service information
	Care connection	Follow-up service	Hospital visit reminders

